## **2.2 Describe the significance of the research, and how it will add to existing knowledge**

Beyond the previous background and justifying the need of the proposed project, the research will have additional significance and impact. Our research would expand the literature on the use of Mediterranean diet interventions in the workplace and among non-Mediterranean populations. A successful intervention would suggest that our approach could be disseminated and implemented nationally in the fire service, as well as potentially among other public safety professions such as law enforcement.

## **3. Study Setting**

### **3.1. Identify the sites or locations where the research will be conducted.**

Indianapolis Fire Department and Fishers Fire Department.

**3.3. Is the research conducted outside the United States?**

☒ No ☐ Yes: If yes; describe site-specific regulations or customs affecting the research, local scientific and ethical review structure

**3.4 Are there any permissions that have been or will be obtained from cooperating institutions, community leaders, or individuals, including approval of an IRB or research ethics committee?**

☐ No ☒ Yes: If yes; provide a list of the permissions (also include copies with the application, if available)

- Chief of Indianapolis Fire Department (IFD) and Indianapolis Local 416 (see attached letters of support). These letters offer the support of the IFD through its Chief and the union through its President (to which the firefighters belong) to participate in the proposed research at the department level. We also provide a similar letter of support from the Fishers (IN) Fire Department. Letter of support and commitment with the analyses of the nested biomarkers study are provided as well (from CSTI, University of Athens and Ohio University award letter to conduct the study.

University of Athens will received the specimens de-identified for urine biomarkers analysis.

Ohio University has already relied on this approved IRB protocol and the documentation is already uploaded.

**4. Study Design****4.1. Describe the study design type**

Prospective, cluster-randomized Mediterranean Diet Nutritional Intervention versus no nutritional intervention for 12 months; followed by cross-over of interventions for an additional 6-12 months. The additional participants from Fishers (IN) Fire Department will be studied for 12 months. The nested study for the evaluation of adherence biomarkers and the stool sample collection will last 6 months.

**4.2. Indicate the study's duration - and the estimated date of study completion**

2 years. December 2018

**4.3. Indicate the total number of participants (if applicable, distinguish between the number of participants who are expected to be screened and enrolled, and the number of enrolled participants needed)**

1,000 career firefighters (500 assigned to group 1 and 500 assigned to group 2). We will approach as many eligible members as possible to consent at least 500 and up to 1,000 participants maximum. For the biomarkers nested study, a total of up to 100 firefighters, selected at random evenly from the existing study arms in Indianapolis

**4.4. List inclusion criteria**

IFD and Fishers members eligible for study consent and participation will include those: a)

permanently assigned to one of the 44 IFD stations or one of the 6 Fishers stations; b) with a fire department-provided medical exam in the last two years; c) at least 18 years of age; and d) full duty, modified or restricted duty status at the time of consent; OR e) Firefighters categorized as “Administrative Staff” by the IFD or Fishers will also be approached for participation and if they consent, be assigned to Group 1 because they are not assigned to specific fire houses.

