## 1. Specific Aims

1. Develop a multi-pronged, Mediterranean Diet Nutritional Intervention (MDNI) behavior change strategies including: diet/lifestyle education; discounted access to key Mediterranean diet foods; electronic education platforms and reminders. MDNI components will be refined via surveys, literature review and local/national firefighter input including labor/management and fire service focus groups.

Hypothesis (1). Cost-effective, fire-service MDNIs will be developed for the cluster-randomized, career firefighter diet intervention.

2. Cluster Randomized Diet Intervention-Phase I- the Indianapolis Fire Department (IFD) has over 1,000 members. All 44 IFD firehouses will be cluster randomized into two groups and then individual members will be consented regarding study participation. Group 1 will receive an active 12-month MDNI, while Group 2 will receive no intervention. Firefighters categorized as "Administrative Staff" by the IFD will also be approached for participation and if they consent, be assigned to Group 1 because they are not assigned to specific firehouses.

3. Cluster Randomized Diet Intervention -Phase II: Group 1 will cross-over to "self-sustained continuation" for 12 months to examine persistence of behavior change during this less intense, self-directed maintenance diet intervention. Group 2 will cross-over to receive the MDNI for 6 months (assessing a shorter MDNI), followed by a final 6 months of self-sustained continuation. An additional neighboring fire department, Fisher's (IN), will have its 6 firehouses randomized to receive the MDNI (Group 3) or no intervention (Group 4) for six months, and then individual members will be consented regarding study participation. After 6 months, the 3 stations in the MDNI (Group 3) will cross-over to "self-sustained continuation" for the last 6 months to examine persistence of behavior change during this less intense, self-directed maintenance diet intervention. Group 4 will cross-over to receive the MDNI for 6 months (assessing a shorter MDNI).

4. A similar 12-month Cluster Randomized Diet Intervention in the six fire stations of the Fishers (IN) Fire Department with a cross-over by the control group to intervention after 6 months will also be done.

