## PHASE I (first 12 months of the study) Group 2: No

### intervention.

#### **Mediterranean Diet Nutritional Intervention for 12 Months for Group 1.**

The extent to which consented participants personally engage in the MDNIs is voluntary, and the additional time commitment required for the study is nominal. The Mediterranean Diet intervention will include educational materials; opportunities for discounted access to healthy foods consistent with the Mediterranean diet (e.g. extra-virgin olive oil, nuts, fruits, vegetables, legumes, whole-unrefined grains, and lean proteins) for both participating firefighters and their families; peer education/support, on-line learning, and email and text message encouragement and reminders. Each of these pieces of the intervention is explained in further detail below.

Educational materials (online learning) will be provided via the study website; group educational sessions and written materials. Examples of our educational information include: a brochure with Mediterranean Diet recommendations, shopping list recommendations and sample recipes, tips to practice the Mediterranean Diet at both home and work and a firefighter-specific Mediterranean Diet Pyramid have been developed for this purpose. These materials may be supplemented as the study progresses to include additional modified Mediterranean Diet recipes based on the firefighters' and their families' preferences and requests (e.g. supply a modified recipe for healthy Mediterranean lasagna or chili based on a fire station's request); short videos; and links to other healthy eating materials. The videos may include: cooking demonstrations; talks with firefighter "champions" (brief interviews and commentaries from firefighters who are successfully practicing the Mediterranean diet) and similar content.

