## PHASE II

### Mediterranean Diet Nutritional Intervention for 6 months for Groups 2 and 3 (and 4 in the final 6 months).

This intervention will be exactly as described above for Phase I, but will last 6 months. Afterwards, over the final 6 months of the study, the participants from Group 2 in Phase 1 will be encouraged to maintain eating Mediterranean style on their own using the support of the discount program, the study website and the support of fellow firefighters and family.

**Group 2: No intervention.** Over the next 12 months (year two). Phase 1 Group 1 participants will be encouraged to maintain eating Mediterranean style on their own using the support of the discount program, the study website and the support of fellow firefighters and family.

The table below summarizes data collection from all consented firefighter participants across the timeline of the 2-year study. Fishers Department FF will be joined to the study in the 12 months of follow up of the original Feeding America's Bravest

| Questionnaires/Measurements        | Baseline | 6months | 12months | 18months | 24 months |
|------------------------------------|----------|---------|----------|----------|-----------|
| Nutrition/Lifestyle questionnaires | X        | X       | X        | X        | X         |
| Blood Pressure                     | X        | X       | X        | X        | X         |
| Height/Weight                      | X        | X       | X        | X        | X         |
| Waist circumference                | X        | X       | X        | X        | X         |
| Body composition (Tanita)          | X        | X       | X        | X        | X         |
| Medical exam results transfer      | X        |         | X        |          | X         |

: .

The table below summarizes data collection from a random subset of consented firefighter participating in the biomarker study

| Biomarker proposal                                   | Time point1
(Dec2017/Jan 2018) | Time point2
(June2018) |
|------------------------------------------------------|-----------------------------------|---------------------------|
| Blood sample collection (fatty acids measurements)   | X                                 | X                         |
| Urine sample collection (hydroxytyrosol and tyrosol) | X                                 | X                         |

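### Section 4.4(e) places Fishers administrative staff in Group 1, a 24-month Indianapolis arm that they cannot complete in their 12 months; the Fishers equivalent is Group 3's schedule

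*Protocol*

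**What the plan says.** **The allocation rule.** Protocol section 4.4, item e, covers administrative staff of both departments: those classed as such "by the IFD or Fishers will also be approached for participation and if they consent, be assigned to Group 1". The reason given is that they belong to no particular station. Section 1, aim 2, gives the same rule and reason with one department named: staff classed as administrative "by the IFD will also be approached for participation and if they consent, be assigned to Group 1". Section 6.1 says that administrative staff of both departments will be approached. It then sends consenting administrative firefighters to Group 1 without naming a department, directly after a sentence on the two Phase 1 arms.

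**Group 1.** Aim 2 forms Groups 1 and 2 by randomising the 44 IFD firehouses. In section 4.6 the first phase is headed "Mediterranean Diet Nutritional Intervention for 12 Months for Group 1" and covers the first 12 months of the study. For year two, the Phase II text says "Phase 1 Group 1 participants will be encouraged to maintain eating Mediterranean style on their own". Aim 3 gives that maintenance period as 12 months.

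**Fishers.** Aim 3 says that this department "will have its 6 firehouses randomized to receive the MDNI (Group 3) or no intervention (Group 4) for six months". Group 3 then has 6 months of self-sustained continuation and Group 4 has 6 months of MDNI. The Phase II part of section 4.6 brings Fishers in at the 12-month point of the original study. Section 4.1 fixes the length: "The additional participants from Fishers (IN) Fire Department will be studied for 12 months".

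**The concern.** Item e decides what a consenting administrative firefighter receives and under which group that person is recorded. For Fishers it names an arm in another department that began a year before Fishers enters and lasts twice as long as Fishers is followed. No other section gives a shortened Group 1 schedule for Fishers or places its administrative staff in Group 3 or 4. Staff obtaining consent at Fishers therefore have a rule that cannot be carried out in full.

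There is also a labelling question. Hypotheses 2-3 in section 1 include a claim that adherence persists better after a 12-month MDNI than after a 6-month one. Group 1 is the only arm with a 12-month MDNI followed by a maintenance period. People recorded in Group 1 who start a year late, without randomisation and without that maintenance period, would have nothing to contribute to that comparison.

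**Working it through.** No sample-size formula is involved. The check is a comparison of timelines, in study months.

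**Inputs**
- Group 1: MDNI for 12 months in Phase I, then continuation for 12 months in Phase II (aims 2 and 3; section 4.6).
- Study duration: 2 years (section 4.2).
- Fishers: enters at month 12 (section 4.6, Phase II) and is studied for 12 months (section 4.1).
- Group 3: MDNI for 6 months, then continuation for 6 months. Group 4: no intervention for 6 months, then MDNI for 6 months (aim 3).

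**Reproducing the stated lengths**
- Group 1: 12 + 12 = 24 months, equal to the stated 2 years.
- Groups 3 and 4: 6 + 6 = 12 months each, equal to the stated Fishers follow-up.

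The schedules are consistent for the people for whom they were written.

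**Putting a Fishers administrative firefighter in Group 1**
- Time available: months 12 to 24, so 24 - 12 = 12 months.
- Time that the Group 1 schedule needs: 24 months.
- Shortfall: 24 - 12 = 12 months.

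| How the assignment is carried out | MDNI months | Continuation months | Group 1 schedule completed? |
|---|---|---|---|
| Joins Group 1 where it then stands (month 12) | 0 of 12 | 12 of 12 | No |
| Starts Group 1 from its beginning at month 12 | 12 of 12 | 0 of 12 (would fall in months 24-36) | No |
| Follows Group 3's schedule instead | 6 of 6 | 6 of 6 | Not Group 1, but 6 + 6 = 12 fits exactly |

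The first row also conflicts with section 7.1, which promises that everyone who consents gets the MDNI at some stage. It gets no support from the Phase II heading in section 4.6 either: "Mediterranean Diet Nutritional Intervention for 6 months for Groups 2 and 3 (and 4 in the final 6 months"). Group 1 is not among the groups listed there for active MDNI. The second row honours section 7.1 but leaves no time after the MDNI in which to observe persistence. The third row honours section 7.1 and fits the time available.

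**The case against.** The strongest reply is that 'Group 1' in 4.4(e) is loose shorthand for starting the MDNI at once. The follow-up part of section 4.6 and section 6.1 both speak of Groups 1 and 2 only, in text that otherwise covers both departments. Section 6.1 presents the choice as immediate or delayed MDNI. Its stated delay of 12 months is the IFD schedule; in Fishers the delay is 6 months. On this view a label was left unrevised when Fishers was added, and these staff were always meant to follow Group 3's schedule. This is probably right about intent, and it is why the point is minor. It does not remove the point: the text names Group 1, and whether these staff receive 12 or 6 months of MDNI depends on that name.

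Three stronger inferences are tempting, and the protocol does not support them.

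- *Aim 2 excludes Fishers staff from Group 1.* It does not. It describes the IFD trial and is silent on Fishers, so the two sections differ in scope. The finding rests on the timelines.
- *These staff would receive no MDNI at all.* That follows only if they join Group 1 in its maintenance year. This is a strained reading, since Group 1 is defined by its active MDNI and section 7.1 says otherwise.
- *The trial's comparisons are biased.* Section 5.1 compares Groups 1 and 2 during the first 12 months, by randomisation of each participant's firehouse. Fishers staff enter after that and have no firehouse. Groups 3 and 4 are formed from stations. No section says that Fishers administrative staff would enter the persistence analysis, and its analysis set may properly be left to a statistical analysis plan.

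It is also fair to say that ending on the MDNI with no later follow-up is already accepted for Group 4, and that IFD administrative staff are likewise placed in Group 1 without randomisation. The latter is a separate matter, which this point leaves as it is.

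**Conclusion.** The concern holds as a minor error in a stated allocation rule. As written, 4.4(e), and 6.1 by implication, send Fishers administrative staff to an arm whose schedule exceeds their follow-up by 12 months, when a 12-month Fishers schedule with immediate MDNI already exists as Group 3. Section 6.1 is the weaker support, because its Group 1 sentence names no department and stands next to the IFD arms.

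The conclusion assumes that Fishers administrative staff enter with the rest of their department at month 12 and leave at month 24; no separate timetable is given for them. That immediate MDNI was intended is an inference from sections 6.1 and 7.1. The number of such staff is not stated. It is probably small, and no effect on any estimate can be calculated. The Group 1 v 2 and Group 3 v 4 comparisons and the power tables in section 5.2 are not shown to be affected.

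**What to change.** In 4.4(e), and in the matching sentence of 6.1, restrict assignment to Group 1 to IFD administrative staff, as aim 2 words it. Add one sentence for Fishers: administrative staff who consent receive the MDNI for 6 months and then 6 months of self-sustained continuation, on the same calendar as Group 3. Record them as non-randomised. State that they do not enter the Group 1 v 2 or Group 3 v 4 comparisons, or the Group 1 side of the comparison of persistence after a 12-month and a 6-month MDNI.

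The cost is a wording amendment, best made before Fishers recruitment. It adds no participants, visits or procedures.

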and longitudinal data analysis, as needed. Differences in the mean values of a quantitative variable between two groups will be assessed using the independent t-test whereas differences in mean values among three or more groups will be examined using the analysis of variance (ANOVA) technique (or non-parametric Wilcoxon and Kruskal-Wallis tests, respectively, as appropriate). Differences in qualitative characteristics will be compared using the chi-square test, or Fisher's exact test, or McNemar's test (for paired comparisons), as appropriate. Statistical significance for all analyses will be  $p < 0.05$ , and all tests will be two-tailed.

Phase 1: During the first 12 months of the nutritional intervention, **groups 1 (Mediterranean Diet intervention) and 2 (no intervention) will be compared directly on an intention to treat basis according to the randomization of each participant's fire house.** As several outcomes will be assessed on each participant throughout the study (3 annual medical exams and 5 semi-annual assessments (where weight, mMDS, etc. will be evaluated)), repeated measures techniques, such as mixed modeling and generalized estimating equation models, will be utilized to estimate changes over time on key outcomes. We will take into consideration the specific variance-covariance structure of correlated measurements. After adjusting for baseline and time-dependent covariates, changes in the outcomes of interest will be assessed and compared among groups. We expect our greatest power to be for within-group changes (paired comparisons).

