## 6. Recruitment Methods

### 6.1. Does the study involve the recruitment of participants?

☐ No: If no, skip to 7.1

☒ Yes: If yes; indicate how, when, where, and by whom participants will be recruited

**6. How:** Up to 1000 IFD members with permanent station assignments at one of the 44 Indianapolis fire houses will be recruited. The initial approach will be through a written announcement from the Chiefs of the Indianapolis Fire Department (IFD)/ Fishers FD and the firefighters' local union presidents (see attached letter) informing the IFD/ Fishers FD of the inauguration of the study and their opportunity to voluntarily participate. Next, human subjects-trained staff from Public Safety Medical (PSM) will visit each fire house to approach IFD/Fishers members for informed consent and determine their eligibility. Their recruitment script is attached. IFD/ Fishers members eligible for study consent and participation will include those: a) permanently assigned to one of the 44 IFD stations or one of 6 Fishers stations; b) with a fire department medical in the last two years; c) at least 18 years of age; and d) full, modified or restricted duty status at randomization; OR e) Firefighters categorized as "Administrative Staff" by the IFD/ Fishers will also be approached for participation. The fire department will notify PSM regarding criteria a, c, d and e and PSM has a record b (medical exams). First, they will provide a brief overview of the study to the firefighters by reiterating the information from the Chief and Union President's letter and the approved informed consent form. They will inform the fire house of its intervention assignment in the study – in other words, whether they will be receiving the nutritional intervention immediately (In Phase 1); or after 12 months (Phase 2). Next, each member will be offered an informed consent form to review on his/her own and will be allowed at least 15 minutes and longer if desired to review it on their own and to discuss it with their colleagues or others. Finally, each member will have a chance to ask the PSM staff questions individually in private areas of the fire house and may decide to sign the form or decline. IFD/Fishers members will be assured that participation status in the study is completely voluntary and will have no bearing on their employment with the department or on the occupational health care they receive from PSM. Consented participants will be assigned to the Phase 1 nutritional intervention (Group 1) or No intervention (Group 2) according to their fire station's cluster randomization. "Administrative" firefighters who consent will be assigned to Group 1 because they are not assigned to specific fire houses. For the biomarkers study randomly 100 participants (50 in each group) will be invited to participate in the study via email at the same time as the follow-up reminder. The recruitment will stop when we reach 60 participants (30 in each group)

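### Administrative staff enter Group 1 without randomisation, and the protocol does not exclude them from the Phase I intention-to-treat comparison

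*Protocol*

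**What the plan says.** The unit of randomisation is the station: "All 44 IFD firehouses will be cluster randomized into two groups and then individual members will be consented regarding study participation" (Specific Aims, item 2). Administrative staff are handled outside that scheme in three places. The Specific Aims say that those who consent will "be assigned to Group 1 because they are not assigned to specific firehouses". Section 4.4 repeats that they will "be assigned to Group 1 because they are not assigned to specific fire houses" and extends the rule to staff so categorised by Fishers. Section 6.1 says that administrative "firefighters who consent will be assigned to Group 1 because they are not assigned to specific fire houses".

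For Phase I, section 5.1 says that Groups 1 and 2 "will be compared directly on an intention to treat basis according to the randomization of each participant's fire house". On adjustment it says: "After adjusting for baseline and time-dependent covariates, changes in the outcomes of interest will be assessed and compared among groups". The covariates are not listed, and staff category is not named.

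The protocol does not exclude administrative staff from the Phase I comparison, assign them to a cluster, or plan an analysis with and without them.

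**The concern.** The allocation rule and the analysis rule do not fit together. The first makes administrative staff members of Group 1. The second analyses Group 1 against Group 2 by a randomisation that these people never had. If they are analysed as Group 1 members, one arm contains a subgroup placed there by job category, and the other arm has nobody of that kind.

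The protocol itself gives reason to expect that this subgroup could respond differently. Much of the programme described in section 4.6 reaches people through stations: small-group sessions in fire-house classrooms and kitchens, station champions, mailers sent to fire houses, and starter foods for fire-house kitchens. Staff with no station differ in setting and perhaps in exposure. Differences in age, rank or fitness are possible, but the document does not describe any.

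At stake is whether the main Phase I contrast rests wholly on randomisation, which is what its description as intention to treat promises.

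**Working it through.** **1. The rules side by side.**
- Who is in Group 1: members of stations randomised to Group 1, plus all consenting administrative staff (Specific Aims, 4.4, 6.1).
- Who is in Group 2: members of stations randomised to Group 2 only.
- How they are compared: by the randomisation of each participant's fire house (5.1). This attribute is undefined for administrative staff.

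**2. What adjustment can do.** Section 5.1 compares changes after adjusting for baseline. A difference in starting level between administrative and station staff would therefore be at least partly absorbed. A difference in 12-month change would not. A staff-category term in the model would take these staff out of the arm contrast, because the category exists in one arm only. That is in effect the same as excluding them, but the protocol does not specify such a term.

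**3. Size of the shift.** Let f be the administrative share of Group 1, and D the mean 12-month change in administrative staff minus that in Group 1 station members.

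Group 1 mean change = (1 − f) × station change + f × (station change + D) = station change + f × D.

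The contrast with Group 2 therefore moves by f × D, in either direction. Neither f nor D is in the protocol, so both are assumptions. The reference is the planned body-fat difference of 1.7 points (section 5.2).

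| f | D (points of change) | Shift f × D | Shift / 1.7 |
|---|---|---|---|
| 5% | 0.5 | 0.025 | 1.5% |
| 15% | 0.5 | 0.075 | 4.4% |
| 5% | 3 | 0.15 | 8.8% |
| 15% | 3 | 0.45 | 26% |

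D = 3 is an extreme bound: as a difference in change it is 3 / 1.7 ≈ 1.8 times the whole planned effect.

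**4. Dependence on sample size.** The shift contains no N, while the standard error falls as N grows. With the planning SD of 6.6 and no clustering, as in the protocol's power table:
- 250 per arm: SE = 6.6 × √(2/250) = 0.590
- 500 per arm: SE = 6.6 × √(2/500) = 0.417

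A shift of 0.075 is 0.13 SE at 250 per arm and 0.18 SE at 500. A shift of 0.45 is 0.76 SE and 1.08 SE. Enrolling more people makes the same shift weigh more in the test.

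**5. Power cost of leaving them out.** First, the protocol's own figure. Power = Φ(1.7 / SE − 1.96), two-sided 0.05. At 250 per arm, 1.7 / 0.590 = 2.88 and Φ(0.92) = 82.1%; the protocol states 82%. At 500 per arm the same formula gives 98.3%, against a stated 98%.

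Now reduce Group 1 to 250 × (1 − f), with SE = 6.6 × √(1/n₁ + 1/250):
- f = 5%: n₁ = 237.5, SE = 0.598, power 81.1%
- f = 10%: n₁ = 225, SE = 0.606, power 80.0%
- f = 15%: n₁ = 212.5, SE = 0.616, 1.7 / 0.616 = 2.76, Φ(0.80) = 78.8%

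At 500 per arm, body-fat power is 98.0% for f = 5% and 97.8% for f = 10%. For metabolic syndrome at 250 per arm, power goes from 75.9% (stated 76%) to 74.7% and 73.4%.

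**6. Fishers.** Section 4.4 sends Fishers administrative staff to Group 1 as well, and section 6.1 can be read the same way. The Specific Aims limit the rule to staff so categorised by the IFD and put the Fishers stations in Groups 3 and 4. Section 4.6 has Fishers joining at month 12, when Group 1 has moved to self-sustained continuation. These statements cannot all hold.

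**The case against.** The strongest reply is that the protocol never says administrative staff enter the Phase I comparison. Section 5.1 ties that comparison to each participant's fire-house randomisation, and taken literally this covers only people who have a fire house. On that reading the analysis set is already the right one. Analysis sets are also commonly detailed in a SAP, which is not at hand. This stands in part: inclusion is inferred from Group 1 membership and the absence of any exclusion. But both the allocation rule and the intention-to-treat rule are set in this protocol, and they support two different answers on who is compared.

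A reader might infer more than the text bears, in three ways.
- That the Phase I result is confounded, or is no longer a randomised comparison. The documents do not support this. All 44 stations remain randomised, inclusion of administrative staff is not stated, and only an unknown share of Group 1 would be affected.
- That any difference in mean body fat between staff types passes straight into the effect, so that 9% to 26% of 1.7 is the expected range. This comes from treating a 3-point difference in level as a 3-point difference in change. Section 5.1 adjusts for baseline and analyses change, so those figures are the high end only.
- That the Fishers wording adds to the Phase I problem. Fishers joins after Phase I, so it cannot.

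It is also fair to say that the allocation is openly stated, with its reason, for people who have no cluster to randomise. That justifies offering them the programme. It does not justify counting them in the randomised contrast.

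**Conclusion.** The concern holds in a limited form. A non-randomised subgroup sits in Group 1 only, and the protocol does not say that it stays out of a comparison described as intention to treat by fire-house randomisation. If it is included, covariate adjustment as written cannot be relied on to remove a difference in change.

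The size and direction of any bias cannot be determined from the document. Under the assumed ranges in the working it runs from negligible (1.5% of the planned body-fat effect) to material (26%, at an extreme value of D). If administrative staff are few or change much as crews do, it is small. The case for acting rests on the conflict in the text and the low cost of resolving it, not on a demonstrated large bias. The Fishers wording is a separate and minor contradiction.

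**What to change.** In section 5.1, define the Phase I intention-to-treat set as consenting participants permanently assigned to one of the 44 randomised IFD stations, analysed by their station's assignment. State that administrative staff are followed and reported as a separate non-randomised cohort, and enter the Group 1 versus Group 2 contrast only in a labelled sensitivity analysis. Align the Specific Aims and sections 4.4 and 6.1 so that receiving the programme with Group 1 is distinguished from belonging to the randomised comparison.

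Separately, reconcile the mention of Fishers in the administrative-staff rule (4.4, and 6.1 where it can be read the same way) with the Specific Aims and the month-12 entry in section 4.6, and state which group Fishers administrative staff belong to.

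The cost is wording and a somewhat smaller Group 1. At 250 per arm, body-fat power goes from about 82% to 80–81% for shares of 5–10%, and to about 79% at 15%; at 500 per arm it stays near 98% for shares of 5–10%. Station randomisation, recruitment and delivery of the programme to IFD staff do not change.
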